### **STUDY DRUG:**

**L-arginine oral administration:** L-arginine (L-arg) is approved for clinical use in MELAS by the Ontario Ministry of Health Inherited Metabolic Diseases Program. A single oral dose of 200 mg/kg of L-arg in normal controls results in a 2.7-fold increase in plasma L-arg at 1 hr, 3-fold increase at 2 hr and sustained 2.4 fold increase at 3 hr after dose, indicating good absorption & time of peak effect & safe plasma maximum of < 200 µM (16). Oral L-arg at 200 mg/kg tid for 6 weeks in a randomized double-blind placebo-controlled study resulted in a sustained increase

Pilot study to investigate the efficacy of L-arginine therapy on endothelium-dependent vasodilation & mitochondrial metabolism in MELAS syndrome.

in exhaled NO (eNO) compared to placebo and was well tolerated. Side effects of L-arg are rare and dose-dependent; low BP, headache, asthma, chest discomfort, nausea, cramps, and diarrhea. Adverse effects to oral L-arg most commonly occur at doses > 30 g/day or 10 g/dose (17). Numerous studies with oral L-arg at 30g/day have reported no gastrointestinal effects (18). Our 4 MELAS sibs have normal lytes, glucose, renal and liver functions & no history of gastrointestinal, respiratory or cardiac problems. L-arg has been well tolerated by most up to 18 mos (3).

Pilot study to investigate the efficacy of L-arginine therapy on endothelium-dependent vasodilation & mitochondrial metabolism in MELAS syndrome.

organic acids to ensure normal values. All control subjects will undergo a urine pregnancy test at the screening visit. A positive test will result in the exclusion of that subject from the study.

### **STUDY DESIGN:**

MELAS sibs will participate in 4 test periods. Controls will be tested at baseline once only with no L-arginine (see Table 1 for Timetable of studies)

(1) **At baseline**, both untreated controls and MELAS siblings will undergo clinical and neurological exams and three sets of tests including (A) quadriceps muscle aerobic cycle ergometry in the magnet using P-MRS with pre- and post- CKs to assess degree of muscle effort and plasma quantitative AA to determine any effect of exercise alone on AA profile, (B) maximal incremental cycle test to investigate overall maximal aerobic capacity with pre- and post- serum CKs and lactates and urine lactate/creatinine ratios to assess degree of effort, and serum quantitative AA and exhaled NO (eNO) to determine any effect of exercise alone on these parameters, and (C) BOLD-fMRI of brain to evaluate CVR with pre- and post- AA to establish a baseline. MELAS sibs and controls will have early morning urine NOx metabolites (nitrites, nitrates) measured to establish their baselines. Plasma AA are measured by our certified HSC Core Lab. As estrogen vasodilates cerebral microvessels by increasing endothelial NOS thus increasing NO (20), we will measure CVR at 0, 4 and 12 wks to coincide with the same phase of menstrual cycle in each of 3 menstruating female sibs and serum estradiol levels will be measured in each subject and their respective age-,menstrual cycle matched controls (21).

(2) **Single Oral L-Arginine Dose Trial:** Four wks after this baseline testing, the MELAS sibs will undergo a trial with a single oral dose of L-arg of 200 mg/kg and will then be retested with the three sets of tests described above. This will allow evaluation of the acute clinical response to a single dose of L-arg and to determine any impact on (a) muscle oxidative function, (b) total body maximal aerobic capacity and (c) CVR. This will also provide an opportunity to evaluate toleration of the dose and any side effects. Tests will be performed at fixed time intervals 60 mins after the oral dose of 200 mg/kg for each MELAS patient to ensure maximum serum L-arg at the time of testing, ending by 2 hrs post-dose. Plasma AA will be measured pre- and post-test procedure to determine the effect of the single oral dose on plasma arg, citrulline and ornithine concentrations as a measure of the efficacy of absorption and to correlate the performance on testing with the concomitant plasma arg concentrations. Following the maximal graded cycle test, (i) exhaled NO (eNO) will be measured to evaluate utilization of L-arg in NO production post oral dose as well as (ii) urinary NO metabolites.

(3) **6 wk Steady State L-Arginine Trial:** If the single oral dose of L-arginine is well tolerated, the MELAS sibs will then be treated with oral L-arginine at 200 mg/kg three times daily (maximum

10g three times daily) for 6 weeks (beginning 2 wks after the single oral dose trial) to assess their clinical response to steady state L-arginine therapy (22,23). The dosage and duration of administration is comparable to studies using similar formulations (3,10,11,16). Preparation of L-arginine will be of high-grade quality prepared by our HSC Institutional Pharmacy according to regulatory standards set by the Ontario Ministry of Health Inherited Metabolic Diseases Program. For the duration of treatment, patients will be evaluated weekly by their pediatrician, Dr. [name] for any adverse events. A medical questionnaire will be completed and full clinical exam including BP. Adverse events will be reported immediately to the PI and External Safety Monitoring Committee composed of a Staff Neurologist with expertise in BOLD-fMRI and Staff Metabolic/Geneticist. If 200 mg/kg is not well tolerated, dosing may be reduced by 50 % to 100 mg/kg 3X daily and the individual reevaluated. After 6 weeks of oral L-arg, MELAS sibs will undergo the same 3 sets of tests to evaluate clinical responses and biochemical parameters to steady state plasma arg levels including clinical and neurological evaluations. L-arg will then be stopped.

**(4) 8-wk Wash-out:** The L-arginine supplementation will be slowly stopped over 6 days time. The schedule for decreasing the dose will be  $\frac{3}{4}$  dose for 2 days,  $\frac{1}{2}$  dose for 2 days and then  $\frac{1}{4}$  dose for 2 days and then stopping the L-arginine. Following discontinuation, the sibs will be seen every 2 weeks by their pediatrician to document any adverse effects upon withdrawal of L-arg. They will be seen for clinical and neurological exams by our Team, 8 wks after withdrawal, and will have baseline biochemical tests to ensure there are no sustained adverse events.

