## **STUDY AIMS**

1. To determine the efficacy and primary mechanism (s) of action of L-arginine in MELAS syndrome by quantifying the effect of L-arginine on (a) cerebrovascular reactivity (CVR) to  $\text{CO}_2$  stimulus (b) neuronal cell activation of CVR and (c) muscle oxidative function in MELAS siblings with the common 3243 A>G mutation.
2. To determine the relative contributions of impaired microvascular endothelial cell function vs impaired neuronal cell activation of CVR in MELAS syndrome.
3. (a) To determine the efficacy of BOLD-fMRI (tool to measure CVR) to differentiate between impaired CVR in a family with variable CNS severity of MELAS compared to controls (b) to determine whether a relationship exists between the severity of neurological phenotype and degree of impairment of CVR as a prognostic predictor for risk of stroke. (\* % mutant mtDNA blood may not correlate with % mutant mtDNA in brain, muscle or heart).

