## **STUDY PLAN**

Brain BOLD-fMRI allows us to examine CVR non-invasively *in vivo* in 4 MELAS sibs vs 4 age-, sex- and menstrual cycle- matched normal controls. To determine the relative contributions of (a) impaired isolated microvascular endothelial cell function in response to changes in  $\text{PCO}_2$  (using a rebreathing circuit) vs (b) impaired occipital neuronal cell (in response to a strong visual stimulus) activation of CVR, we will study both paradigms using brain BOLD-fMRI. Given the variable severity of neurological phenotypes in this family, we will determine the relationship between the severity of the phenotype and the degree of dysfunction in CVR to  $\text{PCO}_2$  vs neuronal stimulus. This correlation may provide a useful tool for predicting the risks for SLEs. To determine the correlation between brain and muscle dysfunction, we will compare brain BOLD-fMRI findings with parameters of total body and muscle oxidative function as determined by maximal incremental cycle ergometry and  $^{31}\text{P}$ -MRS of exercising muscle, respectively. Following these baseline studies, we will then quantify the effect, in only our MELAS sibs, of L-arginine (single oral dose & 6 wk steady state trial) on CVR, neuronal activation, and total body and muscle oxidative function to determine which function(s) is improved. Absorption and exhaled NO production and urine NOx will be measured.

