### **ANALYSIS:**

The following comparisons will be made **(1)** MELAS sibs will be compared to themselves both on L-arginine (single oral dose and 6 wk steady state trial) vs. off L-arginine (pre-trial baseline) to evaluate effects of treatment. **(2)** They will be seen post L-arginine therapy to determine if there are lasting effects up to 8 wks vs. off L-arginine (baseline). **(3)** MELAS sibs at baseline vs. controls **(4)** MELAS sibs on L-arginine (single oral dose and 6 wk steady state trial) vs. controls. Four different end-points will be compared **(A)**  $^{31}\text{P}$ -MRS study of quadriceps for PCr recovery and ATP levels **(B)** maximal oxygen uptake  $\text{VO}_{2\text{max}}$  (ml  $\text{O}_2$ /kg/min) and mean peak work capacity (Watts/kg) **(C1)** CVR to  $\text{CO}_2$  stimulus **(C2)** CVR to neuronal stimulus. Comparisons will be made of the different parameters and to determine whether there are clinically significant differences between the MELAS sib groups (treated vs untreated), and MELAS sib vs control groups (Student's t-test). We understand that the sample size has insufficient power to detect statistically significant differences. However estimates of means and SD's obtained from this pilot study will be used in a future study to determine adequate sample sizes to detect statistically significant differences in these parameters.

**A. P-Magnetic resonance spectroscopy protocol – Muscle function investigation:** We will study exercising quadriceps using our MR-compatible up-down ergometer and our well established aerobic exercise protocol at 65 % of maximal voluntary contraction (25). Testing will be done between 60 to 105 minutes after an oral L-arg dose of 200 mg/kg to ensure maximum serum arg at time of exercise. **Predicted outcome:** Untreated sibs: P-MRS of quadriceps will show a delay in PCr recovery/resynthesis after exercise, reflecting the reduced ATP synthesis rate compared to controls. We predict that the degree of delay in PCr recovery will be directly proportional to the % mutant mtDNA in blood. Following L-arginine, we predict a faster PCr recovery/resynthesis after exercise and increased ATP levels. P-MRS data will be collected on our GE Twin Speed EXCITE™ III 12.0 1.5 Tesla imaging & spectroscopy system at HSC

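### Every on-drug test is a repeat test and no one is retested untreated, so comparisons (1) and (4) mix the L-arginine effect with any retest or time effect and cannot by themselves establish efficacy (Aim 1).

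*Protocol*

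**What the plan says.** Protocol, STUDY AIMS, Aim 1 is worded causally: "To determine the efficacy and primary mechanism (s) of action of L-arginine in MELAS syndrome by quantifying the effect of L-arginine" on cerebrovascular reactivity (CVR) to CO2, neuronal activation of CVR and muscle oxidative function.

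STUDY PLAN sets the groups, "in 4 MELAS sibs vs 4 age-, sex- and menstrual cycle- matched normal controls", and says who is treated: "Following these baseline studies, we will then quantify the effect, in only our MELAS sibs, of L-arginine".

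STUDY DESIGN fixes one order for all sibs. They are tested off drug at week 0. Then: "Four wks after this baseline testing, the MELAS sibs will undergo a trial with a single oral dose of L-arg". After the 6-week course they have the same three test sets again (week 12 in Table 1). For the other group: "Controls will be tested at baseline once only with no L-arginine".

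For the wash-out visit at week 20, STUDY DESIGN item (4) lists clinical and neurological exams and biochemical tests. Table 1 agrees: it adds urine NOx but shows no 31P-MRS, cycle test or BOLD-fMRI.

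ANALYSIS, comparison (1), sets the sibs on drug against their own pre-trial baseline and presents this as the evaluation of treatment. Comparison (4) is "MELAS sibs on L-arginine (single oral dose and 6 wk steady state trial) vs. controls". The same section concedes that the sample is too small for statistical significance and says that the means and SDs will be used to size a future study. HOW DATA WILL BE UTILIZED, item 1, bases the expanded trial on the trends seen here.

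**The concern.** Drug status and test number move together. Each sib's only off-drug endpoint measurement is the first test, and each on-drug measurement is the second or third. The cycle test is maximal and depends on effort, the muscle test is set at a percentage of maximal voluntary contraction in a magnet, and the CO2 test uses a rebreathing circuit. Performance on any of these could shift with practice, effort or elapsed time.

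The people who could show such a shift without drug are the controls, or the sibs after wash-out. Neither is retested on these endpoints. At stake are the efficacy statement in Aim 1, any reading of comparison (4) as a return towards normal, and the effect size taken into the next trial.

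**Working it through.** **Inputs.** From the protocol: 4 sibs and 4 controls; sib endpoint tests at weeks 0, 4 and 12; controls at week 0 only; Student's t-test. Assumed: two-sided 0.05 and a paired test for comparison (1), since alpha and sidedness are not stated; a retest shift δ of 0 to 1.5 SD of within-person change, since the documents give no retest figure. The protocol states no power or alpha figure, so there is nothing to reproduce beyond its qualitative statement of low power.

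**What each comparison estimates.** Let r_j be the shift due to being at test j rather than test 1 (r_1 = 0), d_j the drug effect at test j (d_1 = 0), and g the sib-minus-control difference at the first test.

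- Comparison (1): mean change = d_2 + r_2 at week 4, and d_3 + r_3 at week 12.
- Comparison (4): sibs at test j minus controls at test 1 = g + d_j + r_j.
- Comparison (3): sibs at test 1 minus controls at test 1 = g.

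No scheduled endpoint measurement contains r_2 or r_3 without the matching d. The retest term therefore enters (1) and (4) one for one and does not enter (3).

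**Is the low-power statement right?** Yes. For a paired t-test with n = 4, 80% power needs a true mean change of about 2.1 SD.

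**Effect of a retest shift with an inert drug.** Noncentral t with 3 df, critical value 3.182, noncentrality δ√4 = 2δ. The chance of a positive mean change is Φ(2δ).

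| δ (SD of change) | P(p<0.05) | P(mean change > 0) |
|---|---|---|
| 0 | 5% | 50% |
| 0.25 | 6.5% | 69% |
| 0.5 | 11% | 84% |
| 1.0 | 29% | 98% |
| 1.5 | 53% | >99% |

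With negative δ the table mirrors: the mean change tends downwards and a real benefit is masked.

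**Effect on the next trial.** Illustration only. Suppose a true effect of 0.5 SD of the future endpoint and two arms at 80% power, with n per arm = 2(1.960 + 0.842)²/Δ².

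- Δ = 0.5: 15.70/0.25 = 62.8, so 63 per arm.
- Δ = 0.75 (true effect plus a 0.25 retest shift): 15.70/0.5625 = 27.9, so 28 per arm. Real power is Φ(0.5√(28/2) − 1.960) = Φ(−0.089) = 46%.
- Δ = 1.0: 15.70, so 16 per arm. Real power is Φ(0.5√(16/2) − 1.960) = Φ(−0.546) = 29%.

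**The case against.** The strongest reply is that this is a declared four-person pilot that disclaims significance. That weakens the false-positive argument but does not answer the bias: the disclaimer concerns precision, and more sibs tested in the same order would carry the same retest term.

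Second, the plan is not blind to these issues. It collects CK, lactate and urine lactate/creatinine to judge effort, relates performance to plasma arginine, and times the CVR scans to the same menstrual phase. This stands in part. A reader might infer that nothing collected bears on the problem, and that is too strong. Cycle phase is controlled for CVR, and the markers can flag unequal effort. They still cannot identify a retest effect, and lactate could itself respond to a drug meant to improve oxidative metabolism.

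Third, first exposure cannot be fully verified, because part of the text, including the BOLD-fMRI procedure, is not in the available copy. A practice session may exist. It would reduce familiarisation but would not supply an off-drug retest.

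Fourth, a reader might infer that the order of the off-drug and single-dose tests should be balanced, two sibs each way. The documents do not support this as a good trade:

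- It would put two sibs' off-drug test after dosing and so spoil the first-test-against-first-test basis of comparison (3) and Aims 2 and 3.
- It would give the 6-week contrast a different baseline test number in different sibs.
- The 2-week gap after the single dose precedes more drug, so it is not evidence of wash-out.
- Modelling the period takes the degrees of freedom from 3 to 2. With a standard error of 0.50 SD, the 95% half-width goes from 3.182 × 0.50 = 1.59 to 4.303 × 0.50 = 2.15 SD.
- It changes when two patients are first dosed.

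**Conclusion.** The point holds in a limited form. Comparison (1) estimates the L-arginine effect plus any retest, familiarisation or time effect (other than menstrual phase for CVR), and comparison (4) inherits the same term. The design therefore cannot support "To determine the efficacy and primary mechanism (s) of action of L-arginine in MELAS syndrome" as a conclusion from these contrasts alone.

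The form of the bias follows from the schedule; its amount does not. The rejection rates of 6.5% to 53% rest on assumed shifts of 0.25 to 1.5 SD, a paired test and a two-sided 0.05 level. A reader might infer that the design necessarily favours L-arginine. The documents give no sign for the retest effect, so that does not follow. Nor does it follow that the whole study is compromised: Aims 2 and 3 use baseline data with both groups at the same test number.

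**What to change.** Keep the visit order and change the wording.

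1. STUDY AIMS: restate the efficacy part of Aim 1 as *to estimate the change from off-drug baseline testing during L-arginine, including any retest or time effect*.
2. ANALYSIS: state that comparison (1) is not by itself evidence of efficacy, that comparison (4) is descriptive and not evidence of normalisation, and that the effort markers will be reported beside each on-minus-off change.
3. HOW DATA WILL BE UTILIZED and ANALYSIS: carry the pilot SDs into future sample sizes, but do not use the uncontrolled mean change as the assumed treatment effect.
4. Reconcile the four test periods announced in STUDY DESIGN, and the comparison of lasting effects up to 8 weeks in ANALYSIS, with Table 1, which shows none of tests A to C at visit 4.

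Cost: a less favourable efficacy claim. Items 1 to 3 add no visit, test or patient.

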**B. Maximal Incremental cycle testing to determine total body maximal aerobic capacity:**

Maximal incremental cycle ergometry is conducted in our CardioRespiratory Exercise Lab at HSC by our established protocols (26). Serum CK and quantitative AA (for arginine, ornithine and citrulline) will be measured pre- and post- exercise as well as eNO in order to correlate aerobic exercise parameters with serum arg and eNO levels..Exercise testing will be performed between 60 - 75 min following an oral L-arg dose (200 mg/kg) to ensure maximal serum arg at time of exercise. **Predicted outcome:** Pre-treatment, maximal incremental cycle ergometry will demonstrate a decrease in maximal oxygen uptake  $VO_{2max}$  (ml O2/kg/min) and mean peak work capacity (Watts/kg) which will be directly proportional to % mutant mtDNA (27). We also predict exaggerated circulatory and ventilatory responses to exercise that will increase exponentially in relation to increasing % mutant mtDNA. We anticipate that even though there will be a decrease in O2 uptake by exercising muscle due to defective oxidative phosphorylation, there may be an additional defect, in response to increased exercise demands, related to impaired peripheral vasodilatation, due to endothelial dysfunction of small muscle arterioles. We predict this will respond to L-arg. Alternatively, if aerobic capacity and peak power do not improve with L-arg, this may indicate that endothelium of muscle and heart arterioles is less affected than brain arterioles, given their significantly lower % of mitochondria compared to CNS vessels, and that peripheral vasodilatation is already maximal.

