| 4 MELAS baseline                         | CBC,diff, platelets, lytes, lactate, BUN, Cr, glucose, Ca, PO4, AST, AP, PT, INR, carnitine total/free, estradiol | Pre/post CK, AA
AM Urine NOx             | Pre/post CK, lactate, AA, eNO
urine lactate/creatinine (L/Cr)                                                                                                                                                                                                                                                                                                                  | Pre/post AA
AM urine NOx |
| L-arginine trial                  | Timing of study post-dose                                                                                         | 60-105 min                                  | 60-75 min                                                                                                                                                                                                                                                                                                                                                                         | 75-105 min                  |
| Visit 2–wk 4
Single oral dose | Single Dose Response (60-105 min after oral load)                                                          | Day 1
AM Urine NOx                       | Day 1
PM                                                                                                                                                                                                                                                                                                                                                                       | Day 2
AM Urine NOx       |
| 4 MELAS                                  | Clinical + neurological exam + serum estradiol                                                                    | Pre/post CK, AA                             | Pre/post CK, lactate, AA, eNO, urine L/Cr                                                                                                                                                                                                                                                                                                                                         | Pre/post AA                 |

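### Visit 2 is described as one oral dose, but its two-day timetable and post-dose windows need at least two, so later results and the tolerability condition do not rest on a single dose

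*Protocol*

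**What the plan says.** STUDY DESIGN, item 2, gives the dosing for Visit 2 (week 4): "the MELAS sibs will undergo a trial with a single oral dose of L-arg of 200 mg/kg and will then be retested with" the same three test sets as at baseline. Testing starts 60 min after the dose, "to ensure maximum serum L-arg at the time of testing, ending by 2 hrs post-dose". The visit is meant to show the acute response to one dose and whether that dose is tolerated. Item 3 makes the next phase conditional on it: "If the single oral dose of L-arginine is well tolerated, the MELAS sibs will then be treated with oral L-arginine" for six weeks.

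Table 1 heads the Visit 2 row "Single Dose Response (60-105 min after oral load" (closing bracket follows). It allocates the tests as follows:

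| Test | Day at Visit 2 | Post-dose window |
|---|---|---|
| A. 31P-MRS | Day 1 | 60-105 min |
| B. Maximal cycle test | Day 1 PM | 60-75 min |
| C. BOLD-fMRI | Day 2 | 75-105 min |

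The ANALYSIS text repeats two of these windows. For A: "Testing will be done between 60 to 105 minutes after an oral L-arg dose of 200 mg/kg". For B: "60 - 75 min following an oral L-arg dose (200 mg/kg"). Table 1 also lists plasma amino acids before and after each of the three tests, and morning urine NOx on both days.

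ANALYSIS compares the siblings on and off L-arginine, and with controls, and uses the single oral dose as one of the two treated conditions for every endpoint. Nowhere does the protocol state that the dose is repeated between tests, how far apart doses would be, or which dose the tolerability condition refers to.

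**The concern.** The text and the timetable cannot both be followed. Staff working from STUDY DESIGN would give one dose; staff working from Table 1 would have to give more. Three things depend on which is done.

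- **Label of the results.** If doses are repeated, CVR is read after an earlier dose, and VO2max may be too. Both would still enter the analysis as single-dose results. Their means and SDs are also intended for sizing a later study, so the label would carry forward.
- **Biochemistry.** The Day 2 morning urine NOx comes after Day 1 dosing. Amino acids taken before a later test may not be a clean pre-dose level.
- **Tolerability condition.** Entry to the six-week phase is judged on a single dose that the schedule does not deliver. STUDY DRUG relates adverse effects to amounts both per dose and per day, so the number of doses in a day bears on what is being judged.

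**Working it through.** **Inputs.** One dose of 200 mg/kg and a limit of 120 min post-dose (STUDY DESIGN, item 2). Windows A 60-105, B 60-75 and C 75-105 min, and days Day 1, Day 1 PM and Day 2 (Table 1). The windows for A and B agree with ANALYSIS.

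**Step 1: the plan's own figure.** The stated number of doses is one. With that dose at time 0, every test must lie inside its window. The latest window ends at 105 min, inside the 120 min limit, so the windows agree with that limit. Taken alone, the B and C windows would even fit end to end after one dose (60-75, then 75-105). The conflict comes from the days.

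**Step 2: B and C.** The largest gap under one dose is the end of C's window minus the start of B's: 105 - 60 = 45 min. Even using the general 120 min limit instead, it is 120 - 60 = 60 min. Table 1 puts B on the afternoon of Day 1 and C on Day 2. The protocol gives no clock times. Assuming B between 13:00 and 20:00 and C at 08:00, the gap is:

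- B at 20:00: (24 - 20 + 8) × 60 = 720 min (12 h)
- B at 13:00: (24 - 13 + 8) × 60 = 1,140 min (19 h)

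Either is far above 45 min. One dose cannot serve both tests, so the minimum is **two doses**, 2 × 200 = 400 mg/kg over the visit.

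**Step 3: A and B.** If A comes first, the largest gap under one dose is 75 - 60 = 15 min, while A's window is 105 - 60 = 45 min long. A morning A and an afternoon B therefore cannot share a dose, and the count becomes **three doses**, 3 × 200 = 600 mg/kg over two days. The Visit 2 cell for A says only Day 1; the AM beside it belongs to the urine sample. A morning A is stated only for Visit 1. If both tests were in the afternoon, with B at 60-75 min and A fitted into 75-105 min (30 min), they could share a dose. So three is an inference and two is not.

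**Step 4: what precedes each result.**

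| Result | Two doses | Three doses |
|---|---|---|
| 31P-MRS | first dose | first dose |
| Cycle test, eNO | first dose | second dose |
| Day 2 morning urine NOx | after Day 1 dosing | after Day 1 dosing |
| CVR | second dose | third dose |

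**Step 5: carry-over.** STUDY DRUG gives plasma arginine in normal controls after one dose as 2.7-fold at 1 h, 3-fold at 2 h and 2.4-fold at 3 h. A same-day second dose could therefore start from a raised level. There is no figure beyond 3 h and none for MELAS patients, so an overnight effect cannot be estimated.

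**The case against.** The fairest defence is that single means one acute dose per test session, as opposed to dosing three times daily. ANALYSIS times tests A and B each after *an* oral dose, and Table 1 gives a window per test, which suits that reading. It may be what was intended. But the protocol never says so, and both the design text and the tolerability condition read as one dose.

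A reader might go further and infer that three doses are scheduled, that the endpoints sit on a 200, 400 and 600 mg/kg ladder, and that endpoint is therefore fully confounded with a three-fold difference in exposure. The documents do not support this:

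- The third dose rests on a morning 31P-MRS that is not stated for Visit 2.
- Cumulative mg/kg is the amount given, not effective exposure, and nothing shows Day 1 doses still acting on Day 2.
- Plasma amino acids are taken before and after each test, partly to relate performance to the arginine level at the time. That level is more informative than a dose count.
- Each endpoint is compared with its own baseline and with controls. No planned test ranks endpoints against each other. An earlier dose changes what a Visit 2 contrast should be called; it does not make the contrast invalid.

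The tolerability point also has limits. Even three doses, 600 mg/kg over two days, equal one day of the following phase at 200 mg/kg three times daily before its cap, and adverse events are then reviewed weekly. The visit still informs tolerability; what is unclear is the exposure being judged.

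How dose timing enters the analysis may be set out in a statistical analysis plan. The number of doses at a visit is a protocol matter, and here the protocol contradicts itself.

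**Conclusion.** The contradiction stands. Visit 2 as timetabled needs at least two doses against the one described. This needs no assumption beyond reading Day 1 PM and Day 2 as separate sessions. Three doses follow only if 31P-MRS is in the morning, as at Visit 1.

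On any of these readings CVR follows an earlier Visit 2 dose, the Day 2 urine NOx follows Day 1 dosing, and the tolerability condition names an exposure the schedule does not deliver. VO2max and eNO are affected only on the three-dose reading. The first test remains a true single-dose reading.

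The effect on the results cannot be sized from the documents and may be small. In a four-patient pilot that disclaims power this should be fixed, but it does not undermine the design.

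**What to change.** 1. Reconcile STUDY DESIGN (items 2 and 3), ANALYSIS A and B, and Table 1 on how many doses are given at Visit 2 and when, and on which exposure the tolerability condition refers to. These are decisions for the clinical lead.
2. Record dose number and minutes since the last dose with every Visit 2 result.
3. Use the pre-test plasma arginine already collected to check for carry-over between sessions. The protocol says pre-test, not pre-dose, so state whether that sample comes before the session's dose; only then does it show carry-over directly.
4. Call a result single-dose only if no earlier Visit 2 dose preceded it. Describe the others by the dosing actually given, including when Visit 2 means and SDs are used to plan the later study.

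The cost is protocol and Table 1 wording, two data fields and some relabelling. No extra patients, tests or blood samples are needed.

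### The 10 g per-dose maximum is stated for the 6-week course but not for the Visit 2 single dose or the pre-test doses, so a sib above 50 kg would get a larger first dose than the course dose (minor)

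*Protocol*

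**What the plan says.** - **6-week course** (STUDY DESIGN, item 3): 200 mg/kg three times daily, with a maximum of "10g three times daily) for 6 weeks (beginning 2 wks after the single oral dose trial". This is the only maximum in the visible text.
- **Visit 2** (STUDY DESIGN, item 2): one oral dose of 200 mg/kg, then the three sets of tests. The dose is restated without a maximum: "Tests will be performed at fixed time intervals 60 mins after the oral dose of 200 mg/kg for each MELAS patient".
- **Test sections** (ANALYSIS, A and B): muscle spectroscopy 60 to 105 minutes, and the maximal cycle test 60 to 75 minutes, after 200 mg/kg. Neither gives a maximum, and neither is limited to Visit 2.
- **Dose and side effects** (STUDY DRUG): "Side effects of L-arg are rare and dose-dependent; low BP, headache, asthma, chest discomfort, nausea, cramps, and diarrhea", and "Adverse effects to oral L-arg most commonly occur at doses > 30 g/day or 10 g/dose (17". The same section reports a plasma peak below 200 µM, which it calls safe, after a single 200 mg/kg dose in normal controls.
- **Role of Visit 2** (STUDY DESIGN, item 3): it gates the course. "If the single oral dose of L-arginine is well tolerated, the MELAS sibs will then be treated with oral L-arginine".
- **Step-down** (STUDY DESIGN, item 3): "If 200 mg/kg is not well tolerated, dosing may be reduced by 50 % to 100 mg/kg 3X daily".

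**The concern.** The course maximum matches the protocol's own adverse-effect levels, so it looks like a deliberate safeguard. It has any effect only above 50 kg, which means the protocol itself allows for a sib of that weight. Yet for such a sib the safeguard is absent at the first study exposure, which is also the tolerance check and is followed about an hour later by a maximal exercise test.

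Two things follow for a sib above 50 kg. The first dose is larger than any dose in the course. And the tolerance check tests a different dose from the one it is meant to clear. Passing is still informative, because the sib has tolerated at least the course dose. Failing is less so: intolerance of 12 or 14 g does not show that 10 g would not be tolerated.

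**Working it through.** **Inputs.** Dose rate 0.2 g/kg (STUDY DESIGN, items 2 and 3). Course maximum 10 g three times daily (item 3). Adverse-effect levels above 10 g per dose or 30 g per day (STUDY DRUG). Step-down 0.1 g/kg (item 3). Body weights are not shown; those below are assumptions.

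**The plan's own figure.** 10 g × 3 = 30 g per day. The course maximum therefore sits exactly at both levels named in STUDY DRUG.

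**Weight at which the maximum begins to act.** 10 g ÷ 0.2 g/kg = 50 kg.

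**Dose by weight.** Uncapped dose = 0.2 × weight. Capped dose in mg/kg = 10,000 mg ÷ weight.

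| Assumed weight | Visit 2 dose as written | Excess over 10 g | 10 g expressed in mg/kg |
|---|---|---|---|
| 40 kg | 8 g | none | maximum not reached |
| 50 kg | 10 g | none | 200 |
| 60 kg | 12 g | 2 g (20%) | 167 |
| 70 kg | 14 g | 4 g (40%) | 143 |
| 80 kg | 16 g | 6 g (60%) | 125 |

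**Number of such doses.** Table 1 spreads the Visit 2 tests over Day 1 and Day 2, each timed after a dose, so at least two doses are implied. If Day 1 needs one for the spectroscopy and another for the afternoon cycle test, the Day 1 total is 2 × 12 = 24 g at 60 kg and 2 × 14 = 28 g at 70 kg. It passes 30 g only above 30 ÷ 0.4 = 75 kg. The per-dose level is thus the one that is crossed first.

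**If Visit 2 is not tolerated and the step-down is used.** 0.1 × 60 = 6 g and 0.1 × 70 = 7 g per dose, that is 18 to 21 g per day. This is 60% to 70% of the capped 10 g dose (30 g per day).

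**The case against.** The case for leaving the text alone has five parts.

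- *It may affect nobody.* The four sibs are identified in advance and the investigators know their weights. The protocol lists poor growth among the features of MELAS. If all four are at or below 50 kg, nothing changes. This stands, and it makes the point conditional. Part of the text between STUDY DRUG and STUDY DESIGN was also not available for review and could hold weights or dosing detail.
- *The uncapped dose has a stated basis.* STUDY DRUG cites a single 200 mg/kg dose with good absorption and a safe plasma peak, and the test timing is built on that profile. This stands in part. Those data come from normal controls, and the same section still gives the 10 g per-dose level.
- *The 10 g figure is not a hard limit for one dose.* The protocol says where adverse effects are most common and calls them rare. A cap on six weeks of dosing three times a day does not strictly contradict an uncapped single dose. This stands: the gap is one of consistency and precaution, not a logical contradiction.
- *Under-dosing after a failed check is not dictated.* The step-down is worded as an option, with the individual then re-evaluated. A reader might infer that a heavier sib who failed at 12 or 14 g must go to 6 or 7 g. The text does not say so; it is only possible.
- *A cap departs from uniform mg/kg exposure* in a small mechanistic pilot that wants peak arginine at testing. This is a real cost, but the protocol already accepts the lower mg/kg dose for the course.

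**Conclusion.** The point holds in a limited form. In the visible text, the 10 g maximum covers the 6-week course only. A sib above 50 kg dosed as written would receive a first dose 20% (60 kg) to 40% (70 kg) above both the course dose and the protocol's own per-dose adverse-effect level. Severity is minor. It rests on two assumptions: that at least one sib exceeds 50 kg, and that no maximum for these doses stands in text that was not available.

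Two stronger readings are tempting and are not supported. Because the listed side effects include low blood pressure and chest discomfort and a maximal exercise test follows, a reader might infer that the plan exposes a sib to expected harm. The protocol calls side effects rare, regards the plasma peak after 200 mg/kg in controls as safe, and does not tie those effects to 12 to 14 g. A reader might also infer that the week-12 pre-test dose overrides the cap. The aim there is to "evaluate clinical responses and biochemical parameters to steady state plasma arg levels", so the natural reading is that the sib takes the current course dose; only a clarification is needed.

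**What to change.** Write *200 mg/kg (maximum 10 g per dose)* for the Visit 2 dose in STUDY DESIGN, item 2, and for the pre-test doses in ANALYSIS, sections A and B. The tolerance check then uses the same dose as the course. As a clarification, add that the week-12 pre-test dose is the sib's current course dose, whether capped or reduced.

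The cost is a few words in three places and one sentence, with no change to visits, tests or endpoints. Sibs at or below 50 kg are unaffected. The downside is that a sib of 60 to 70 kg would receive 143 to 167 mg/kg at Visit 2, below the 200 mg/kg behind the cited absorption profile. The sampling already planned would show the level reached: "Plasma AA will be measured pre- and post-test procedure to determine the effect of the single oral dose".
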